### Harms {17}

The intervention paradigm, cognitive bias modification for interpretation (CBM-I), has been evaluated in over 100 trials and has consistently been found to be safe and no riskier than standard care [7]. The primary potential harm is temporary distress during task completion for the intervention group when reading content which could trigger depressive thoughts. Prior feasibility data on the predecessor of CURED, CBM-Errors, indicated that participants’ immediate mood was typically unaffected or slightly improved following sessions [12]. Adverse Events (AEs) information will be proactively collected at the 3-week check-in call using an adapted version of the Adverse Events Checklist, and an exit interview will provide a further opportunity for adverse event data gathering. If a participant experiences persistent mood deterioration, distress impairing daily functioning, or any indication of risk to self or others, participation will be paused, a risk assessment made and, if appropriate, clinical care will be arranged (e.g. referral to the participant’s GP or mental health team). All AEs judged to be serious, according to the standard HRA definition, will be reported to the Sponsor and REC in line with governance requirements. All adverse events will be presented descriptively by frequency, relatedness to the intervention, severity and seriousness to provide comprehensive safety data which will be reported in trial outputs.

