***Feasibility measures***					
Credibility/Expectancy Questionnaire (CEQ)		X		X	
Exit Questionnaire					X

^a^Arrow indicates continuous delivery of the assigned condition

^b^C/bal stands for counterbalancing, which was used alternate item content across multiple timepoints to prevent order effects. The specific counterbalancing schedule is available upon request

^c^The interim (i.e. weekly) assessments are completed only after completing the intervention/control session of that week

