### Criteria for discontinuing or modifying allocated intervention/comparator {15b}

Participants may discontinue or be discontinued if adverse events (AEs), serious adverse events (SAEs), or mood worsening are identified at any point during the study and deemed related to the study procedures. This is assessed using an adverse events checklist (see Harms {17} for more information).

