### Strategies to improve adherence to intervention/comparator {15c}

Adherence to the allocated intervention or control condition will be supported and monitored through structured participant contact. At the first session, a researcher will conduct an orientation call to explain procedures and address any questions. Weekly email reminders will be sent to encourage ongoing engagement, with additional reminders if sessions are missed. A scheduled check-in call will take place at week 3 (mid-point) to assess mood, review progress, troubleshoot difficulties, and reinforce adherence. Researchers will also conduct calls at each main assessment point (baseline, post-intervention, and 12-week follow-up) to support participation and ensure data completeness.

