### Outcomes {16}

#### Primary outcomes

As this study is a feasibility evaluation of the CURED intervention, there is no single primary clinical outcome. Instead, (1) feasibility, (2) acceptability, (3) blinding integrity, and (4) safety will be assessed across several domains. These metrics will inform progression criteria for a future definitive RCT.*Feasibility* will be quantified using response, recruitment, eligibility, and randomisation rates; adherence; retention; and weekly assessment completion rate.*Acceptability* will be assessed using quantitative measures (Credibility and Expectancy Questionnaire; Exit Questionnaire) and qualitative interviews exploring user experience, barriers, and facilitators to engagement.*Blinding integrity* will be evaluated by the success of randomisation, percentage of unblindings, and by examining whether participants and researchers can correctly guess allocation at the final 12-week follow-up (last contact point).*Safety* will be evaluated throughout the trial by monitoring and documenting adverse events (AEs) and serious adverse events (SAEs), with frequency, severity, and relatedness recorded at each assessment point.

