### Plans to promote participant retention and complete follow-up {25b}

Participants will receive reminder emails or text messages for each session and before each interim and main assessment, alongside sustained contact with the research team through regular calls at baseline, week 3, post-treatment (week 6), and the 12-week follow-up. To acknowledge participants’ time investment, reimbursement will be provided in line with their level of involvement: a total of £80, divided into four instalments of £20 following completion of (1) the baseline assessment, (2) the first three weekly assessments, (3) the post-treatment assessment, and (4) the 12-week follow-up assessment. Retention will also be supported by the research team remaining available during online assessments to address any technical or procedural questions without interfering in responses.

Participants will be retained in the study wherever possible, even if they initiate therapy or medication during the trial. Participants may opt to continue with outcome assessments only, as an alternative to complete study withdrawal.

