### Data management {26}

This study will generate both quantitative (self-report questionnaires, experimental tasks at baseline, post-treatment, and 12-week follow-up) and qualitative data (semi-structured exit interviews at post-treatment) in both paper and electronic format. Electronic data will be stored on secure King’s College London servers, hosted through King’s cloud services. The main datasets will be prepared in both R and SPSS formats, with approximately 60 cases expected. Paper materials (i.e. booklets) will be stored in locked filing cabinets within secure university premises, accessible only to authorised members of the research team.

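### Harms {17} places the adverse event checklist at the week-3 call and adds an undefined exit interview, while Outcomes {16} has events recorded at every assessment point

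*Protocol article*

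**What the plan says.** Outcomes {16} lists safety among the primary outcomes and has AEs and serious AEs monitored throughout, "with frequency, severity, and relatedness recorded at each assessment point".

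Harms {17} describes collection differently: "Adverse Events (AEs) information will be proactively collected at the 3-week check-in call using an adapted version of the Adverse Events Checklist". It then adds that "an exit interview will provide a further opportunity for adverse event data gathering", giving no date, number of participants or arm for that interview.

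The discontinuation criteria in {15b} depend on the same tool and send the reader to the same section: "This is assessed using an adverse events checklist (see Harms {17} for more information").

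Researcher contacts are described in two places. Section {25b} lists "regular calls at baseline, week 3, post-treatment (week 6), and the 12-week follow-up". Section {15c} treats week 3 as a mid-point check-in and lists the main calls separately: "Researchers will also conduct calls at each main assessment point (baseline, post-intervention, and 12-week follow-up"). It gives the purpose of those main calls as supporting participation and complete data, and does not mention AEs.

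Data management {26} dates one kind of exit interview: "qualitative data (semi-structured exit interviews at post-treatment"). Section {27a} plans qualitative interviews with 8 participants, all in the intervention arm. The same section tabulates AEs and serious AEs by arm, with frequency, severity and relatedness.

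**The concern.** A by-arm AE table can be interpreted only if both arms were asked the same question at the same times. Sections {16} and {17} do not describe the same collection plan. A team working from {16} would record events at weeks 6 and 12. A team working from {17} would give the checklist once, at week 3, and rely on an interview whose coverage is not defined.

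Two things are at stake. First, {17} names temporary distress while reading CURED content as the main potential harm, but the one dated checklist comes about halfway through six weekly sessions. Later sessions and the six weeks of follow-up have no stated structured enquiry that reaches everyone. The plan also relies on continuous monitoring of risk when it explains why no data monitoring committee is needed ({28a}). Second, if the exit interview is held in one arm only, events after week 3 would be sought more actively in that arm, and the table could show a difference that comes from the asking.

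**Working it through.** The plan gives no figure to reproduce. The check sets the sections side by side and counts who is asked.

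**Inputs.** 30 per arm, 60 in total ({19}). Researcher calls after baseline at weeks 3, 6 and 12 ({15c}, {25b}). Proactive checklist at week 3, plus an exit interview ({17}). Qualitative exit interviews at post-treatment ({26}). Qualitative interviews with 8 intervention-arm participants ({27a}).

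**Step 1: structured enquiry stated in {17}.** Of the three post-baseline calls, one has a stated proactive AE enquiry. For anyone without an exit interview, the stretch from week 3 to week 12 is 12 − 3 = 9 of 12 weeks.

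**Step 2: what the exit interview adds.** Its recipients and date are open, so three readings are set out. Target numbers are used, with no drop-out.

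| Reading of the exit interview in {17} | Week 3 | Week 6 (CURED / control) | Week 12 (CURED / control) |
|---|---|---|---|
| The 8 qualitative interviews, at post-treatment | 60/60 | 8/30 / 0/30 | none stated in {17} |
| Everyone, at post-treatment | 60/60 | 30/30 / 30/30 | none stated in {17} |
| Everyone, at week 12 with the Exit Questionnaire | 60/60 | none stated in {17} | 30/30 / 30/30 |

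None of the three gives a structured enquiry to every participant at both week 6 and week 12. Only the first treats the arms differently: 8/30 = 27% against 0%. Section {16} still asks for recording at both times, but does not say how events are to be elicited.

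**Step 3: size of the arm difference, first reading only.** Let p be the probability that a participant has an event between weeks 3 and 6, the same in both arms and in those interviewed. Let s be the share of such participants who report it unprompted. The document gives neither, so the ranges are assumptions: p from 5% to 20%, s from 0 to 0.5.

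- Expected recorded in CURED: 8p + 22ps. In control: 30ps. True number per arm: 30p.
- Excess in CURED: 8p + 22ps − 30ps = 8p(1 − s).
- s = 0: CURED 0.4 to 1.6, control 0, of 1.5 to 6.0 true cases per arm. Share recorded: 8/30 = 27% against 0%.
- s = 0.5: CURED 0.95 to 3.8, control 0.75 to 3.0. Share recorded: (8 + 11)/30 = 63% against 50%.

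The expected excess therefore runs from 0.2 (p = 5%, s = 0.5) to 1.6 participants (p = 20%, s = 0). If everyone is interviewed at post-treatment, both arms record 30p and the excess is zero.

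**The case against.** The strongest reply is that the two sections do not exclude each other. Section {17} never says the checklist is used at week 3 alone. Recording whatever comes to light at every assessment, with one structured checklist in mid-treatment, is a coherent scheme. Under {25a} a researcher is on a video or telephone call while participants complete the assessments, so events can be recorded at weeks 6 and 12. The full protocol, not shown here, may say how they are elicited. This stands in part: a reader might infer a flat contradiction, and the text does not go that far. It does not remove the mismatch, because {15b} relies on {17} for the checklist and {17} dates that checklist only at week 3.

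A reader might also infer that nobody is asked about AEs after week 6. The documents do not support this. Section {16} calls for recording at the 12-week assessment, and the undated exit interview could fall at week 12, where the Exit Questionnaire sits.

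Nor do they support the inference that AE collection is unequal between the arms. That needs the exit interview in {17} to be the 8-person interview in {27a}, a link the article never makes.

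The lack of an AE row in Table 2 is weak evidence, since the table also omits the week-3 call and the qualitative interviews, and the flow diagram in Fig. 3 cannot be seen. Weekly PHQ-9 and mood scales, the BDI-II and the global rating of change may prompt reports in both arms, but they do not record AEs with severity and relatedness.

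**Conclusion.** The point holds as a mismatch that should be settled. For a primary outcome tabulated by arm, {16} and {17} describe different collection plans, and {17} leaves the recipients and timing of the exit interview open. Followed as written, the plan states a structured AE enquiry for all participants at one of three post-baseline calls, and none for all participants at both week 6 and week 12. That conclusion needs no assumption about event rates.

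The arm difference of 8/30 against 0/30 is conditional on an unstated link. Even then, under the assumed ranges, the expected excess is 0.2 to 1.6 participants, in descriptive tables with no hypothesis tests. The case for acting is that the ambiguity bears on a primary outcome and is cheap to remove. There is no demonstrated bias.

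**What to change.** State one schedule in {16}, {17} and Table 2: the blinded researcher gives the same AE checklist to every participant in both arms at the existing week-3, week-6 and week-12 calls. Base the by-arm AE table on these checklists plus spontaneous reports. List events first mentioned in the intervention-arm qualitative interviews separately, outside the by-arm counts. State in {17} who has the exit interview and when.

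As recruitment has started, report how many participants in each arm were asked at each time point, so that the table can be read correctly for those enrolled before the change.

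The cost is two more short checklists per participant, at most 60 × 2 = 120, within calls already planned, together with one added row in Table 2 and a wording amendment. The cross-reference in {15b} can stay, and no new contacts or staff are needed.

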### Participant timeline {18}

Table 2 and Fig. 3 describe the participant flow in the trial.

**Fig. 3 Fig3:**
[figure not shown]
The CONSORT flow diagram of the feasibility trial procedure

### Sample size {19}

As this is a feasibility trial, formal power analysis was not appropriate. Consistent with recommendations that feasibility studies include approximately 25–35 participants per arm [36–38], we set our target sample size at 30 participants per arm (60 participants in total).

### Recruitment {20}

Potential participants will be identified through a) South London and Maudsley (SLaM) Consent for Contact (C4C) register, after permission is gained for direct approach from the relevant clinician b) advertising (e.g. King’s College London curricular research newsletter; SLaM’s *Take Part in Research* newsletter) c) the McPin Foundation and d) self-referral via the study website (www.curedtrial.co.uk). For routes b-d potential participants will be asked to email a dedicated study enquiry address ([contact]). Upon receiving an enquiry, the recruitment team will respond by sending the Participant Information Sheet (PIS) and inviting the individual to schedule an initial research call for consent and screening, ensuring at least 24 h for consideration. Those meeting eligibility criteria during this call will then be scheduled for an online baseline assessment, after which participants will be randomised. Participants will receive the relevant intervention materials by post at the start of the week following randomisation.

## Assignment of interventions: randomisation

### Sequence generation: who will generate the sequence {21a}

The random allocation sequence will be generated and overseen by a randomisation team (CF, JY, EU) who are not part of the patient-facing research team and not otherwise involved in trial delivery. The randomisation team is responsible for creating and maintaining the randomisation file and communicating identifier codes.

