### Eligibility criteria for sites and those delivering interventions {14b}

This trial will be conducted at a single site under the lead of the Chief Investigator (JY), a site investigator (KK; a clinical researcher and PhD candidate), and the Project Coordinator (CF). Recruitment and intervention delivery will be undertaken by a team comprising post-graduate research assistants (RAs), MSc students, and the clinical researcher (KK).

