### Implementation {23}

Blinded researchers contact the randomisers by email notifying them of a new enrolment. Randomisers assign the next available PIN and provide the relevant sealed envelopes to researchers for weekly posting. Sealed envelopes are then posted by the blinded researchers to participants according to the weekly schedule.

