### Procedure for unblinding if needed {24c}

Unblinding may be requested by the Chief Investigator or Sponsor. In the unlikely case of a team member becoming aware of a clinical emergency (e.g. serious self-harm, suicide, risk of harm to others, psychiatric hospital admission involving a participant) that could be related to the intervention or study procedures, or where there is uncertainty, the following steps will be taken:Team member reports to the Chief Investigator within 24 hChief Investigator consults with the Sponsor, if needed, within 48 hIf unblinding is required, the participant’s allocation will be disclosed by the randomiser team accessing the randomisation file which holds details of the assigned conditionAll instances of unblinding will be documented and reported to the Sponsor who advises on the need to report to the HRA.

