#### Pseudonymisation and security

Each participant will be assigned a unique Participant Identification Number (PIN), used both on electronic records and paper booklets. All paper records will carry only participant identification numbers (PINs) and no personal identifiers. All datasets will be stored using these PINs, while the master list linking PINs to personal identifiers (name, contact details) will be kept separately on a secure drive, password-protected at the individual file level, and accessible only to the Chief Investigator (custodian of the trial data). During the active trial, data will remain pseudonymised; after analysis and UK data archive deposit, the master list will be destroyed (estimated August 2026), rendering the data fully anonymised.

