## Oversight and monitoring

### Composition of the coordinating centre and trial steering committee {3d}

The coordinating centre for this trial is the research team based at King’s College London, Department of Psychosis Studies, who are responsible for day-to-day management and operational support, including recruitment, randomisation, data collection, and data management.

A Project Management Group (PMG) will act in place of a formal Trial Steering Committee and provide both operational and higher-level oversight of the trial. The PMG is responsible for supervising trial conduct, reviewing study progress, and recommending amendments or actions where required. Weekly operational meetings are held to review recruitment progress, address questions or issues arising, and discuss topics requiring immediate attention. PMG meetings are attended by the randomisation team, recruitment team, and the Chief Investigator (CI), all based at King’s College London, and are jointly led by the CI, Project coordinator, and the clinical researcher site lead.

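### Two of the three unblinded randomisers lead the trial, so the stated independence of the randomisation team does not hold, and nothing in the article says adverse events are rated blind

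*Protocol article*

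**What the plan says.** Section {21a} of the protocol article says the allocation sequence is generated and overseen by three people, identified by initials, who are "not part of the patient-facing research team and not otherwise involved in trial delivery". Section {24a} says these three are unblinded and everyone else is blinded. Section {22} gives them sole access to the allocation file, has them prepare the sealed envelopes and has them receive the returned booklets.

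Section {14b} uses two of the same sets of initials for the trial's leaders: "This trial will be conducted at a single site under the lead of the Chief Investigator", together with a site investigator and the Project Coordinator. Section {3d} says the Chief Investigator, the Project Coordinator and the site lead jointly lead the PMG. The PMG supervises conduct, may recommend amendments and takes the place of a steering committee. On attendance it says: "PMG meetings are attended by the randomisation team, recruitment team, and the Chief Investigator (CI".

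On emergencies, {24c} says "Unblinding may be requested by the Chief Investigator or Sponsor". It routes clinical emergencies that could be related to the study to the Chief Investigator within 24 hours, with the Sponsor consulted if needed.

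On identity, the pseudonymisation paragraph of {26} says the master list linking PINs to names and contact details is "accessible only to the Chief Investigator (custodian of the trial data". Section {33} lets authorised team members see personal identifiers. Section {23} says of the PIN-labelled materials: "Sealed envelopes are then posted by the blinded researchers to participants according to the weekly schedule".

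**The concern.** A reader judging concealment and blinding relies on {21a} for assurance that those who know the allocation are separate from those who run the trial. If two of the three are its leaders, the article claims a safeguard that the design lacks.

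Blinding integrity and safety are two of the four primary outcome domains in {16}. Under {27a}, the frequency, severity and relatedness of adverse events are presented by arm. Relatedness is a judgement, and it is open to bias if the person making it, or someone that person consults first, knows the arm. Knowledge could also pass from unblinded leaders to blinded recruiters without being noticed or recorded. The blinding results in {27a} list recorded unblindings and participants' guesses, and neither is aimed at that route.

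**Working it through.** No formula applies and the plan gives no figure to reproduce. The check sets the sections side by side.

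1. **Who the randomisers are.** {21a} and {24a} list three sets of initials. {14b} attaches two of them to the Chief Investigator and the Project Coordinator. So 2 of 3 randomisers are trial leads. The third has no role in {14b}.

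2. **What {21a} claims.** It makes two statements: no part in the patient-facing team, and no other involvement in trial delivery. The first agrees with {14b}, which gives recruitment and intervention delivery to research assistants, MSc students and the clinical researcher. The second comes on top of the first, so it must exclude more than participant contact. Leading the trial ({14b}) and the group that supervises its conduct ({3d}) does not fit it.

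3. **Who leads the PMG.** There are three joint leads, of whom the Chief Investigator and the Project Coordinator are unblinded: 2 of 3. Its meetings bring unblinded randomisers and blinded recruiters together, and {3d} states no separation of agenda items.

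4. **Where functions coincide.**
   - Allocation access ({22}, {24a}): Chief Investigator, Project Coordinator and third randomiser.
   - PIN-to-identity list ({26}): Chief Investigator only.
   - First receipt of possibly related emergencies ({24c}): Chief Investigator.

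   All three meet in one person, the Chief Investigator. The Project Coordinator has the first only.

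5. **Who rates events.** {17} says when adverse events are collected (the week-3 call and the exit interview) and {27a} says how they are tabulated. Neither says that the rater of severity or relatedness is blinded.

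6. **Whether the PIN list rule can be followed.** Under {22} the envelopes carry only PIN and week number. Under {23} blinded researchers post them. Posting requires matching a PIN to an address, which is the content of the list that {26} restricts to the Chief Investigator. {33} describes wider access to identifiers. The three sections do not describe one workable arrangement.

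7. **What would detect leakage to staff.** {16} plans to examine whether participants and researchers can guess the allocation at 12 weeks. The matching list in {27a} names participants' guesses only. The measure that could reveal leakage to blinded staff is announced in one section and absent from the other.

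**The case against.** **Narrow reading.** Trial delivery in {21a} could mean only the recruitment and intervention delivery that {14b} assigns to others, and {24a} openly says the three are unblinded. This stands in part: nothing contradicts the statement about patient-facing work, and a careful reader can work out the overlap. But under the narrow reading the second clause adds almost nothing to the first, and a reader of {21a} alone is misled.

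**Protection elsewhere.** Blinded staff enrol participants and see only sealed envelopes ({23}, {24b}). Apart from screening and the MINI depression module, the assessments are self-report ({25a}). Serious events go to the Sponsor and the ethics committee ({17}), which also oversee risk monitoring ({28a}). All of this stands and limits the consequence.

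**Separate objects.** The master list in {26} and the identifiers in {33} may be different files. That is possible, but posting by PIN still needs the link between them.

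Some stronger readings are tempting but not supported:

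- *Blinding is broken, or would be reported as intact when it is not.* No section shows leakage. {16} plans researcher guesses, and {24b} requires any researcher unblinding to be recorded.
- *Blinded and unblinded staff discuss participants every week.* {3d} describes weekly operational meetings on recruitment, issues and urgent topics, and mentions PMG attendance separately. It neither equates the two nor says that individual participants are discussed. Multiplying weeks of recruitment into a number of mixed meetings is therefore unsafe, and recruitment opened on 16/07/2025, before the first randomisation on 18/08/2025. A count of meetings would not measure leakage anyway.
- *The Chief Investigator rates adverse events, or receives all of them.* {24c} covers clinical emergencies only, and no section names the rater.
- *The request step in {24c} is itself an error.* A documented request is compatible with holding the file. It simply does not restrain someone who already has access.

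**Conclusion.** The contradiction between {21a} and {14b}, {24a} and {3d} holds: the randomisation team does not have the independence claimed for it. Its size is structural: two of three randomisers lead the trial, two of three PMG leads are unblinded, and three sensitive functions meet in the Chief Investigator. It bears on two of the four primary outcome domains. It is a risk to blinding and to unbiased rating of events, and does not show that either has failed. It should be corrected, but it does not invalidate the trial.

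The conclusion rests on two assumptions. One is that matching initials denote the same people. The other is that the full protocol, not shown here, does not already provide for blinded rating of adverse events. If it does, that part reduces to adding a sentence. The conflict between {26}, {22}, {23} and {33} over the PIN list is a smaller, separate inconsistency in the same arrangement.

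**What to change.** 1. Correct {21a} to say that the Chief Investigator and the Project Coordinator are unblinded randomisers who also lead the trial, and that the team has no patient-facing role.
2. Have a blinded team member record the severity and relatedness of each adverse event before it reaches anyone with allocation access. The record should be made within the reporting times already in {24c}, which this point does not seek to change.
3. Keep randomisers out of participant-level items in any meeting attended by blinded staff, and say so in {3d}.
4. Reconcile {26} with {22}, {23} and {33}, so that the blinded staff who post and call hold the PIN-to-identity list and those with allocation access do not.
5. Add the researchers' allocation guesses named in {16} to the blinding analyses in {27a}, so that leakage to staff can be seen.

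The cost is a short amendment, a change in who holds the PIN list and one extra recording step per event. Taking the allocation file away from the two leaders is not required: it could not re-blind people who already know allocations.
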